#### Objective

The central objective of this trial is to design optimal adaptive combinations of vector control interventions to maximize reductions in malaria burden based on local malaria transmission risks, vector ecology, and the available mix of interventions approved by the Ministry of Health of Kenya.

#### Trial design

This is an open-label, block-cluster randomized, controlled, sequential multiple assignment trial with a variable number of arms (adaptive design) and a baseline period without crossover. A potential trial design is shown in Fig. 1 and Table 1.

**Fig. 1 Fig1:**
[figure not shown]
Study site; distribution of trial clusters and initial interventions. Block zones are shown in different background colors; initial intervention in each cluster is shown in different boundary colors. LLIN, long-lasting insecticidal net; PBO, piperonyl butoxide-treated LLIN; IRS, indoor residual spraying

**Table 1 Tab1:**
[figure not shown]
Content and timelines for the schedule of enrolment, interventions, and assessments

*Due to the adaptive nature of the design, the initial interventions (year 1) are fixed; however, the subsequent interventions depend on the outcomes from initial interventions, i.e., effective interventions will be continued; otherwise, other interventions will be introduced. Black color represents definite interventions, and red color represents all possible interventions depend on outcomes from previous stage of interventions. *LLIN* long-lasting insecticidal net, *PBO LLIN* piperonyl butoxide-treated LLIN, *IRS* indoor residual spraying, *LSM* larval source management

**Enhanced method: the most cost-effective method determined by machine learning based on outcomes from previous interventions

#### Interventions

##### LLIN

We will use the currently implemented LLINs, which are the standard intervention administrated by the MoH. These include Olyset LLIN (Sumitomo Chemical UK PLC, London, UK), which contains 2% permethrin with 150 denier yarn, and PermaNet 2.0 (Vestergaard, Lausanne, Switzerland) containing 1.8 g/kg (75 denier yarn) or 1.4 g/kg (100 denier yarn) of deltamethrin. For LLIN clusters, no additional nets will be supplied, since this intervention is the government-administered standard intervention and current coverage is very high (95%) in our study area. In addition, local government-run hospitals, clinics, and health centers routinely distribute nets to pregnant women and children under 5 years old, and therefore, the coverage is well maintained.

##### PBO LLIN

We will test the Olyset Plus LLIN (Sumitomo Chemical UK PLC, London, UK), which contains 2% permethrin and 1% PBO. For the PBO Net clusters, each household will be provided one Olyset Plus per two people along with appropriate education, which is the same as the standard LLIN allocation practice [2, 3]. Residents will be asked to use the PBO Nets provided, and net usage will be monitored.

##### Actellic® IRS

For the IRS, we will use the micro-encapsulated pirimiphos-methyl, Actellic 300CS (Syngenta Crop Protection AG, Basel, Switzerland), with an AI concentration of 300 g/L. Actellic 300CS IRS has been implemented in several African countries [35, 50–52]. For IRS clusters, each dwelling’s interior walls and ceiling will be sprayed with the recommended dosage of 1 g/m^2^ at the recommended frequency of once a year. This is also the current PMI-implemented spraying frequency in several African countries [50–52].

##### LSM

LSM will be implemented in selected clusters and will include the physical filling or removal of temporary larval habitats and the larviciding of semi-permanent and permanent habitats, per Kenya’s National Malaria Strategic Plan [2, 3]. For the larviciding, we will use the long-lasting microbial larvicide manufactured by Central Life Sciences (Sag Harbor, NY, USA) with active ingredients *Bacillus thuringiensis israelensis* (Bti) (6% by weight) and *Bacillus sphaerius* (Bs) (1% by weight). This product has been proven effective against insecticide-resistant mosquitoes [34]. Application dosage will follow the recommendation of the manufacturer: semi-permanent and permanent habitats will be treated with FourStar® 180-day Briquets with one briquet per 100 ft^2^ of water surface, regardless of water depth. Re-treatment will occur every 4 to 5 months.

#### Primary and secondary endpoints

The primary endpoint is clinical malaria incidence rate. The secondary endpoints are malaria vector abundance and transmission intensity. A clinical malaria case is defined as an individual with fever (axillary temperature of 37.5 °C or higher) and other related symptoms such as chills, severe malaise, headache, or vomiting, in the presence of a *Plasmodium*-positive blood smear. Clinical malaria incidence rate is calculated as the number of clinical malaria episodes divided by the total person-time (person-years) at risk based on demographic surveys. Malaria vector abundance is measured as the total density of malaria vector mosquitoes (*An. gambiae* s.s., *An. arabiensis*, *An. funestus*, and other new species capable of transmitting malaria) collected indoors by CDC miniature light traps. Malaria transmission intensity is measured as the sum of the indoor entomological inoculation rates (EIRs).

### Study area and cluster selection

We will conduct our study initially in 36 randomly selected clusters in an area consisting of both low- and high-elevation localities (1100 m to 1700 m altitude) in the Lake Victoria shore area southeast of Kisumu County, western Kenya (34° 49′ E to 34° 59′ E, 0° 15′ S to 0° 22′ S) (Fig. 1). A cluster is a village or several neighboring villages, typically covering an area of approximately 2 km^2^ and comprising 200–300 households and about 500–1000 inhabitants. A village is the smallest administrative unit in Kenya. For simplicity of management and field surveys, cluster boundaries will coincide with administrative boundaries. These boundaries have been mapped using ArcGIS prior to any field surveys based on Kisumu County administrative maps. Clusters are selected at about 2 km apart to avoid any spill-over effect. The catchment population of the study area, including all study clusters and buffer zones, is estimated as 100,000 according to 2010 census data.

Local residents are predominantly farmers who depend on crop farming and cattle and goat herding for subsistence. Malaria transmission is seasonal, with two peaks in vector abundance reflecting the bimodal rainfall pattern: a major peak between April and June and a minor peak between October and November [53]. Malaria is predominantly caused by *Plasmodium falciparum* [54]. The main malaria vectors in the area are *An. gambiae* s.s., *An. arabiensis*, and *An. funestus* s.l. [55]. In the trial study area, a 2017–2018 survey found that *An. funestus* accounted for 45% of all *Anopheles* captured, followed by *An. gambiae* s.l. (37%), and other *Anopheles* species (18%), and 89% of *An. gambiae* s.l. are *An. arabiensis* [50]. In addition, outdoor transmission is high [50, 55]. The mosquito resistance to different insecticides which include pyrethroids has been reported in the study area and in the nearby Ahero area (10 km north of the trial site) [8, 50]. Although metabolic-based resistance has not been determined in the study area, the fact that *An. funestus* is the dominant malaria vectors in the area justifies the usefulness of PBO LLINs, because pyrethroid resistance in *An. funestus* is due mainly to metabolic-based resistance [56].

### Baseline surveys for cluster randomization

We will conduct entomological, epidemiological, and demographic surveys before the start of the interventions (Table 1). Together with other topographic and landscape variables, these surveys will provide baseline data for cluster stratification and randomized allocation of different interventions. The baseline data will also be used in evaluating the interventions.

#### Demographic and socioeconomic data

A baseline census of the population with house locations (mapped by spatial coordinates) will be conducted at the start of the study and updated annually. Demographic surveys will include all residents who live inside the study clusters. Each household and its family members will have a unique ID that will be used to trace the individuals’ visits to health centers for cross-sectional blood sampling and active malaria case surveillance. We will use our pre-established demographic surveillance system to track the population and its changes on an annual basis.

Data on socioeconomic status and malaria intervention practices will be obtained during the demographic surveillance, which will administer a separate questionnaire to all households in each study cluster. A series of questions will address socioeconomic status indicators (house size, ownership of electronics, land income, occupation, and others), LLIN ownership and usage, use of repellents, use of IRS, and malaria treatment-seeking behaviors.

#### Cross-sectional vector abundance and malaria infection prevalence

To determine malaria infection prevalence, cross-sectional finger-prick blood samples will be collected on blood films and on filter papers for PCR analysis, following the nested PCR method for dried blood spots based on the 18S rRNA gene to detect the malaria species [54, 57, 58]. In western Kenya, the major rainy season is usually from April to July and the major dry season is from November to March next year. To minimize the seasonality effect, we will conduct vector abundance and parasite prevalence surveys twice a year, once in June/July and another time from November to January.

All clusters will be examined for mosquito abundance. We have previously determined that the CDC light trap is an efficient sampling tool [55, 59]. For each cluster, we will conduct adult mosquito collections in 10 houses for 10 nights per month. *An. gambiae* s.l. and *An. funestus* s.l. will be analyzed by rDNA-PCR for species identity [60, 61]. All specimens will be tested for *Plasmodium* sporozoite infection using PCR [62, 63], and blood meal analysis will be performed by PCR [64–66]. Aquatic habitats within the 0.5-km buffer zone of the study cluster will be mapped using GPS and examined for *Anopheles* larval and pupal abundance using standard dippers [67]. A subset of larvae will be reared to adults and used to test resistance to pyrethroid and organophosphate insecticides using the standard WHO insecticide susceptibility bioassay [68]. *Plasmodium falciparum* isolates from the community-based and hospital-based surveillance will be genotyped at *Pfmdr*1 for lumefantrine tolerance and at *PfKelch*13 for artemisinin resistance [69].

#### Acquisition of other malaria risk predictor variables

A variety of predictor variables for malaria risk will be collected for each cluster: (1) human density and age structure; (2) topographic parameters, which are associated with mosquito larval habitat formation [70, 71]; (3) land-use and land-cover types related to the development and survival of Anopheline mosquito larvae and adults [72–74]; and (4) meteorological data. Topographic parameters such as elevation, slope, wetness index, flow distance to stream, aspect of land surface, and curvature will be obtained from the digital elevation model of the study site, which we have already developed. Land-use and land-cover data will be obtained from supervised classification of the most recent satellite images, and the normalized difference vegetation index (NDVI) will be computed. Meteorological data (temperature, rainfall, and vapor pressure) will be obtained from a global 0.5° × 0.5° gridded data set of monthly terrestrial surface climate from the World Meteorological Organization database.

### Cluster stratification for interventions

For each cluster, we will determine vector abundance and malaria infection prevalence. Malaria risk in each cluster will be predicted based on the predictive features (variables) described above. We plan to adopt two approaches for risk prediction. The first approach (classification-based) will first stratify the study clusters into distinct strata based on weighted vector abundance and malaria infection prevalence using *k*-means or hierarchical clustering algorithms [75]. A classifier will be trained to predict risk-group assignments based on predictive variables. To avoid overfitting, we will first try classification models with low complexities, such as naïve Bayes, softmax, and support vector machines (SVM) to establish a baseline, and then move to more complex models, such as decision trees, random forests, and neural networks [76–81]. The second approach (regression-based) will directly predict prevalence and malaria transmission intensity based on the predictive variables using Gradient Boosting (GB) linear and logistic regression (LogitBoost) or an ensemble of regression trees [82]. Each method has pros and cons. The classification-based approach is easier to interpret and less prone to overfitting, but the cluster assignment may not be clear-cut. On the other hand, although it does not require cluster assignment, the regression-based approach must model prevalence and vector abundance separately and is thus more prone to overfitting with nonlinear models [83].

The data from all study clusters (36 initially) will be split into a training set and a validation set, with model parameters trained on the training set and performance evaluated on the validation set. Tenfold cross-validation will be performed to maximally utilize the data [84, 85]. For the classification task, we will determine each model’s sensitivity and specificity and use the auROC (area under ROC curve) to measure model performance. For the regression task, we will use the mean-square loss to measure model performance. Trained models will be further tested and refined on data from 36 different clusters collected in year 2 and future years.

The goal is to stratify all clusters into 3 blocks during the initial intervention stage: low transmission, intermediate transmission, and high transmission.

### Trial design and outcome measures

#### Initial cluster randomization

The SMART trial design includes two intervention stages (Fig. 2 and Table 1). Based on pre-intervention malaria risk analysis, study clusters will be stratified into three blocks with different risk levels as described above. In each block, clusters will be randomly assigned with equal probability to one of the three interventions in stage 1, i.e., LLIN, PBO LLIN, and LLIN + IRS (Fig. 2). Cluster randomization will be done using computer-generated random numbers. Ideally, each block will include 12 clusters and each of the three interventions will be assigned to four clusters in each block (Fig. 1).

**Fig. 2 Fig2:**
[figure not shown]
Sequential multiple assignment randomized trial (SMART) study for developing adaptive malaria intervention strategy in Kenya. R, randomization; LLIN, long-lasting insecticidal net; PBO LLIN, piperonyl butoxide-treated LLIN; IRS, indoor residual spraying; LSM, larval source management

#### Stage 1 intervention

Stage 1 (initial intervention) will be 15 months long, including a 3-month field implementation of interventions and 12 months of follow-up on the interventions’ impact. The main purpose of stage 1 is to determine the effect of the individual interventions on malaria incidence and to identify clusters not responding to these interventions. At the beginning of stage 1, all study clusters will be randomized with equal probability to the three interventions, as shown in Fig. 2, by a block randomization method. At the end of the 12-month follow-up, clusters will be assessed for “response” versus “non-response” to PBO Nets or LLIN + IRS. Response and non-response are defined based on the change in clinical malaria incidence when using PBO Nets/LLIN + IRS compared to LLIN (Fig. 2). If a cluster demonstrates a reduction in malaria incidence that is (1) statistically significant and (2) greater than the pre-defined threshold value set by the Ministry of Health (MoH) based on cost-effectiveness, then this cluster is considered a responder; otherwise, the cluster is considered a non-responder. It is important to use the LLIN group (group A in Fig. 1) as the comparison group when determining response/non-response, because malaria incidence varies between seasons and years due to seasonal or inter-annual climatic variability. In addition, LLIN is the government-implemented first-line routine intervention.

#### Stage 2 intervention

The stage 2 intervention will be 21 months long, including a 3-month intervention implementation and 18 months of follow-up on the interventions’ impact. The main objective of stage 2 is to identify the optimal adaptive intervention in clusters not responding to the stage 1 intervention, i.e., the non-response clusters at the end of stage 1 will receive a modified intervention to improve the outcome (reduction of malaria incidence) (Fig. 2). In particular, non-responders to stage 1 PBO LLIN treatment will be randomized with equal probability to either PBO LLIN + LSM (larval source management) or an intervention determined by an enhanced reinforcement learning method. Similarly, non-responders to stage 1 LLIN + IRS treatment will be randomized with equal probability to either LLIN + IRS + LSM or PBO LLIN + IRS. Therefore, this design has 4 embedded adaptive interventions (Table 2).

**Table 2 Tab2:** Four embedded adaptive interventions in the proposed SMART trial study

Embedded adaptive intervention	First-stage intervention	Status at end of first-stage treatment	Second-stage intervention option	Subgroup in the design
#1	PBO LLIN	Responder	Continue PBO LLIN	B + C
		Non-responder	PBO LLIN + LSM	
#2	PBO LLIN	Responder	Continue PBO LLIN	B + D
		Non-responder	Enhanced machine learning method	
#3	LLIN + IRS	Responder	Continue IRS	E + F
		Non-responder	LLIN + IRS + LSM	
#4	LLIN + IRS	Responder	Continue IRS	E + G
		Non-responder	PBO LLIN + IRS	

#### Enhanced machine learning method

A reinforcement learning-based method will be developed and deployed to adaptively assign treatments to different study clusters based on stage 1 intervention results and historical results. Assume *K* treatment options are available and each treatment’s outcome (*a*) is stochastic, depending not only on treatment but also on contextual cluster features (*s*) such as current malaria prevalence, incidence rate, and the socioeconomic, entomological, and genetic features described earlier. We will use a specific reinforcement learning algorithm, *Q*-learning [86], to design a function, *Q*(*s*, *a*), which calculates the expected reward (e.g., reduction of malaria incidence) if treatment *a* is applied to the study group with feature vector *s*. The *Q*-function measures each treatment method’s effectiveness conditioned on specific clusters and will be learned based on data collected from existing and ongoing trials. We will use linear functions, decision trees, or neural networks to model the *Q*-function [81, 87]. To avoid overfitting, we will start with simple linear models and progress toward more complex models such as decision trees and neural nets when more data become available. The enhanced method will automatically assign a treatment to each group based on the estimated *Q*-function. To achieve a balance between exploration and exploitation, we will assign treatments stochastically according to a probability vector calculated from the *Q*-function. A number of algorithms are possible, including **ε**-greedy, Boltzmann exploration, upper confidence bounds (UCB), and reinforcement comparison [88]. We will first test these algorithms in simulation studies and choose the best one for implementation in real trials.

#### Sample size justification

The primary aim of this study is to determine which initial intervention, PBO LLIN or LLIN + IRS, is more effective in reducing malaria incidence after 36 months. The second aim is to estimate the mean outcomes of the 4 embedded adaptive interventions from months 16 to 36 and to identify the most effective intervention. Sample size calculation is based on the primary aim, using the primary outcome (clinical malaria incidence) and between-group comparison of the average clinical malaria incidence at month 36. The proposed sample size (*n* = 36 clusters) will detect a 10% reduction in clinical malaria incidence with 89.2% power using the current incidence rate in the study sites (302 clinic cases per 1000 person-years) and a 2-tailed *α* = 0.05 with a human population size of 500 per cluster (Table 3). If malaria incidence is 30% lower than the current value, the design will still detect a 20% incidence reduction with 97% power (Table 3). This calculation assumes a 1:1 response/non-response ratio, a fixed cluster size of 500 participants, and an intra-cluster correlation coefficient of 0.05 [89]. This sample size is likely powered to detect smaller changes in incidence reduction, as previous studies in Kenya and Ghana indicated intra-cluster correlation coefficients of < 0.02 [90].

**Table 3 Tab3:** Power calculation (%) for proposed cluster-randomized SMART trial. Shown are degrees of power to detect four levels of incidence reduction under three incidence scenarios

Annual incidence rate (cases/1000 population)	Reduction in malaria incidence			
	40%	30%	20%	10%
Observed in the site: 302	> 99.9	> 99.9	> 99.9	89.2
30% lower value: 211	> 99.9	99.8	97.0	59.0
30% higher value: 393	> 99.9	> 99.9	> 99.9	97.0

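### The 89.2% power for PBO LLIN versus LLIN + IRS takes the current standard-net incidence as its reference rate, which is optimistic for a contrast between two active arms

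*Protocol article*

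**What the plan says.** All places are in the protocol article.

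- **Primary aim** (Sample size justification): to "determine which initial intervention, PBO LLIN or LLIN + IRS, is more effective in reducing malaria incidence after 36 months". The standard-LLIN arm is not part of this contrast.
- **Basis of the calculation** (same section): "Sample size calculation is based on the primary aim, using the primary outcome (clinical malaria incidence"), compared between groups at month 36.
- **Reference rate and power** (same section): the trial "will detect a 10% reduction in clinical malaria incidence with 89.2% power using the current incidence rate in the study sites", given as 302 per 1000 person-years.
- **Response** (same section): "This calculation assumes a 1:1 response/non-response ratio".
- **Table 3**: for a 10% reduction, power is 89.2% at 302, 59.0% at 211 and 97.0% at 393. The 211 and 393 rows are labelled as 30% lower and 30% higher incidence. The text cites the 211 row only for a 20% reduction (97%).
- **What lies behind the current rate** (Interventions, LLIN): "this intervention is the government-administered standard intervention and current coverage is very high (95%) in our study area". LLIN clusters receive no extra nets.
- **Definition of response** (Stage 1 intervention): "Response and non-response are defined based on the change in clinical malaria incidence when using PBO Nets/LLIN + IRS compared to LLIN". The reduction must be statistically significant and must exceed a cost-effectiveness threshold.
- **After stage 1** (Stage 2 intervention): non-responding clusters move to a modified intervention intended to improve their outcome.

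**The concern.** In a two-arm power calculation the reference rate is the incidence expected in the arm that does worse. Here both arms are active, but the rate used is the one observed under standard nets. If background transmission stays as it is, 302 can be the reference only if the weaker of PBO LLIN and LLIN + IRS averages no gain over LLIN up to month 36.

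That does not fit two other parts of the plan. Half of the clusters are assumed to respond, and response means a significant reduction against LLIN. Non-responders then have their intervention changed after month 15 to bring incidence down further. Both features put the expected rate in each active arm below 302.

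At a fixed relative difference, a lower reference rate means fewer cases and less power. A reader who takes 89.2% at face value would treat a null PBO LLIN versus LLIN + IRS result as more informative than it is.

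**Working it through.** **1. Inputs.** Reference rate 302 per 1000, two-sided α = 0.05, 500 people per cluster, ICC 0.05 and 1:1 response come from Sample size justification. Twelve clusters per arm (four in each of three blocks) comes from Initial cluster randomization. The effect of either active arm against LLIN is not given, so it is varied below.

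**2. Can the stated 89.2% be reproduced?** No.

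- Design effect = 1 + 499 × 0.05 = 25.95. Effective n per arm = 12 × 500 / 25.95 = 231.2.
- For 0.302 versus 0.2718: variance sum = 0.302 × 0.698 + 0.2718 × 0.7282 = 0.4087; SE = √(0.4087 / 231.2) = 0.0420; z = 0.0302 / 0.0420 = 0.718; power = Φ(0.718 − 1.96) = 10.7%.
- With a Poisson variance, power is 8.8% for one year of person-time and 18.1% for three.
- With no clustering at all, the two-proportion figure is 95.5%. Reaching 89.2% with 12 clusters per arm needs an ICC of about 0.0006.

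No variant tried reproduced the Table 3 cells together, so the comparison and formula behind 89.2% cannot be identified.

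**3. Consistency of 302 with the 1:1 assumption.** If half of an arm's clusters achieve a reduction x against LLIN and the rest achieve none, the arm mean is 302 × (1 − x/2). This is below 302 for any x > 0. As an illustration, x = 20% gives 302 × 0.90 = 272. Any stage 2 benefit lowers it further.

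**4. How much power is lost if 89.2% is accepted at 302?** Two methods, both for a 10% relative difference:

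- *Interpolating Table 3.* z = 1.96 + Φ⁻¹(power) gives 3.197 at 302 and 2.188 at 211. For rate r, z = 2.188 + 1.009 × (r − 211) / 91.
- *Holding effective n fixed.* The n giving 89.2% is 3.197² × 0.4087 / 0.0302² ≈ 4,581 per arm. It is then applied at the lower rates.

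| Weaker arm's reduction against LLIN (assumed) | Reference rate | Interpolated | Fixed n |
|---|---|---|---|
| 0% | 302 | 89.2% | 89.2% |
| 10% | 272 | 82% | 84% |
| 20% | 242 | 72% | 79% |
| 30% | 211 | 59% (printed) | 71% |

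The methods differ because the Table 3 cells follow no standard formula. In the 211 row the implied z values for 10/20/30% reductions are 2.19, 3.84 and 4.84. A two-proportion test matched to the first cell would give 2.19, 4.47 and 6.87.

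**5. The same rates with the stated clustering** (effective n 231.2, binomial variance, normal approximation):

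| Reference rate | 10% | 20% | 30% | 40% |
|---|---|---|---|---|
| 302 | 10.7% | 31.0% | 61.1% | 86.5% |
| 272 | 9.8% | 27.5% | 55.2% | 81.6% |
| 242 | 9.0% | 24.3% | 49.1% | 75.5% |
| 211 | 8.2% | 21.1% | 42.9% | 68.4% |

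If between-cluster variation is instead a constant coefficient of variation (0.34), the reference rate hardly matters: 92.3% at 302 and 91.6% at 211 for a 40% difference.

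**The case against.** - **A reader might infer that 89.2% was really computed for an active arm against LLIN.** The document does not support this. It ties the calculation to the primary aim, and because the figure cannot be reproduced, what was computed is unknown. The point is an optimistic reference rate, not a proven wrong comparison.
- **A reader might infer that the power is too high by construction.** It is not. The reference rate also depends on background transmission, which the protocol says varies by season and year. If background incidence were 393, an active arm with a 23% reduction would sit at 302 (302 / 393 = 0.77). This objection stands, which is why the conclusion is limited to unchanged background transmission.
- **Table 3 already has a lower row.** It does, and power at a given rate is the same whatever lowered it. But that row is offered as a lower-incidence scenario, the 59.0% is not discussed in the text, and the headline remains 89.2%.
- **At the stated ICC the reference rate matters little for a 10% difference.** True: 10.7% against 8.2%. The clustering problem is larger. The reference rate still matters at detectable differences under binomial variance (86% against 68% for 40%), so a recalculation that kept 302 would carry the problem forward.

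**Conclusion.** The concern holds in limited form. The 302 reference rate is optimistic for an active-versus-active contrast and does not sit with the 1:1 response assumption or with stage 2. This assumes that background incidence stays near its current level.

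The size of the loss is conditional. Accepting 89.2% at 302, a 10–30% effect of the weaker arm takes power to somewhere between 84% and 59%, depending on effect and method.

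It may be tempting to quote 59–83% as the corrected power, but the documents do not support that range. The lower end assumes a 30% effect that no section states. The upper end (an arm mean of about 277) needs an invented test of one cluster against 12 pooled LLIN clusters. The whole range also inherits a starting figure that is incompatible with the stated ICC.

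**What to change.** 1. Stop presenting 89.2% as the power for PBO LLIN versus LLIN + IRS.
2. State the incidence assumed in the weaker active arm as 302 × (1 − assumed reduction against LLIN), consistent with the 1:1 response assumption. Rows at 272, 242 and 211 would cover reductions of 10%, 20% and 30%.
3. Recompute Table 3 at those rates with 12 clusters per arm and the stated ICC of 0.05, and name the formula and the variance assumption.
4. Label the 302 row as active versus LLIN only if the sponsor confirms that this was the comparison computed.

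The cost is a rewritten paragraph and a recomputed table. No clusters, data or procedures change, but the stated power will be much less favourable.

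### The stated power (89.2% for a 10% reduction) and Table 3 do not reflect the stated intra-cluster correlation of 0.05; at the plan's own inputs, unadjusted power for a 10% reduction is about 11%

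*Protocol article*

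**What the plan says.** All the inputs are in the protocol article, most of them under Sample size justification.

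- Primary aim: "to determine which initial intervention, PBO LLIN or LLIN + IRS, is more effective in reducing malaria incidence after 36 months". The sample size rests on this aim, through a "between-group comparison of the average clinical malaria incidence at month 36".
- Result claimed: 36 clusters "will detect a 10% reduction in clinical malaria incidence with 89.2% power using the current incidence rate in the study sites", at "a 2-tailed *α* = 0.05". The reference rate is 302 cases per 1000 person-years. A second claim is 97% power for a 20% reduction if incidence is 30% lower (211 per 1000).
- Assumptions named: a 1:1 split of responders and non-responders, "a fixed cluster size of 500 participants, and an intra-cluster correlation coefficient of 0.05".
- Table 3 gives power for reductions of 40, 30, 20 and 10% at three incidence levels. Every entry is 97.0% or higher except 89.2% (302, 10%) and 59.0% (211, 10%).
- The section closes by saying that smaller changes are probably detectable too, because earlier studies found ICCs below 0.02.

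Under Initial cluster randomization: "Ideally, each block will include 12 clusters and each of the three interventions will be assigned to four clusters in each block". Three blocks of four give 12 clusters per initial intervention, so the primary contrast uses 24 of the 36 clusters.

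**The concern.** An ICC of 0.05 with 500 people per cluster is a heavy penalty: it leaves roughly one twenty-sixth of the nominal sample. A 10% relative difference from 302 per 1000 is about 30 per 1000 in absolute terms, and 12 clusters per arm would not be expected to resolve that with nearly 90% power.

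The sample size is justified by this calculation alone. If the printed power is not what the stated assumptions give, readers are told that the trial can tell PBO nets from LLIN + IRS at a difference far smaller than those assumptions allow.

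**Working it through.** **Inputs** (from the sections above): rates 0.302 and 0.302 × 0.9 = 0.2718; m = 500; ICC = 0.05; 12 clusters per arm; two-sided alpha 0.05. My assumption is that one year's incidence is treated as a proportion. The responder ratio does not alter the number of clusters in each initial arm.

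**1. Attempt to reproduce 89.2%**
- With no clustering, 12 per arm: z = 0.0302 / √[(0.302×0.698 + 0.2718×0.7282)/6000] = 3.66, power 95.5%. A Poisson variance gives 87.0%.
- With no clustering, 9 per arm: 88.6% for the 302 row and 97.1% for the 393 row (stated 89.2% and 97.0%). The 211 row is then 70.6% and 99.9% (stated 59.0% and 97.0%).
- With 0.05 read as a correlation between 36 monthly measures (design effect 2.75 on 18,000 person-years per arm): 89.7% and 95.7% for the 302 and 393 rows, but 76.9% for the 211 row.

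No variant tried reproduces the whole table.

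**2. Power at the stated inputs**
- Design effect: 1 + 499 × 0.05 = 25.95.
- Effective number per arm: 6000 / 25.95 = 231.2.
- Standard error: √[(0.302×0.698 + 0.2718×0.7282)/231.2] = 0.0420.
- z = 0.0302 / 0.0420 = 0.72.
- Power: 11.1% counting both tails, 10.7% counting only the correct direction. A t reference on 22 df gives 10.6%.

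**3. Table 3 recomputed**, 12 against 12 clusters, proportions, no adjustment (stated value in brackets):

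| Rate per 1000 | 40% | 30% | 20% | 10% |
|---|---|---|---|---|
| 302 | 86.5 (>99.9) | 61 (>99.9) | 31 (>99.9) | 11 (89.2) |
| 211 | 68 (>99.9) | 43 (99.8) | 21 (97.0) | 9 (59.0) |
| 393 | 96 (>99.9) | 77 (>99.9) | 43 (>99.9) | 14 (97.0) |

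**4. Other readings of the 302, 10% cell that keep the design effect of 25.95**
- Poisson variance: 9%.
- 12 against 24 clusters: 13%.
- All 36 clusters split 18 against 18: 14%.
- Three-year cumulative risk: 13% (12 per arm) or 17% (18 per arm).
- Design effect applied to three-year person-time: 18,000/25.95 = 694 per arm, z = 0.0302/√[(0.302+0.2718)/694] = 1.05, power 18%; with 18 per arm, 25%.

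The range is about 9% to 25%. Larger clusters do not help: as cluster size grows without limit, the 10.7% rises only to 11.0%.

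**5. ICC needed for the stated figures.** Power of 89.2% needs z = 1.960 + 1.237 = 3.197. The design effect can then be at most (3.659/3.197)² = 1.31, so ICC = 0.31/499 = 0.0006. At ICC 0.05, 89.2% would instead need about 238 clusters per arm.

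**6. Lower ICCs**, rate 302, 12 against 12:

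| ICC | Power, 20% reduction | Power, 10% reduction | Reduction detectable with 80% power |
|---|---|---|---|
| 0.05 | 31% | 11% | 37% |
| 0.02 | 61% | 20% | 25% |
| 0.01 | 86% | 32% | 18% |

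**7. The 211 row on its own.** The stated 59.0% at a 10% reduction implies z = 1.960 + 0.228 = 2.19. A 20% reduction doubles the difference, and the standard error cannot rise because the lower rate has the smaller variance. So z must be at least 4.37, which is power of 99.2% or more. The table prints 97.0% (z = 3.84). The implied standard errors are 0.0211/2.19 = 0.0096, 0.0422/3.84 = 0.0110 and 0.0633/4.84 = 0.0131 for 10, 20 and 30% reductions. They rise where they should fall slightly. This check needs no assumption about the ICC or the number of clusters.

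**The case against.** The strongest reply has four parts.

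**The table may not have been calculated without clustering.** A reader might infer that Table 3 simply ignores the ICC. The documents do not show this. In the 211 row, an unclustered 12 against 12 calculation gives 82% (proportions) or 73% (Poisson) at a 10% reduction, well above the printed 59.0%, so something lowered that row. The method source is cited, not shown. This stands: one can say only that the table does not reflect the stated ICC.

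**The 11% is an unadjusted figure.** Clusters are blocked into three risk strata (Cluster stratification for interventions) and the analysis adjusts for malaria risk (Data analysis), so the residual ICC should be below the raw one. This also stands, and 11% should not be read as the design's final power. It does not rescue 89.2%, which needs a residual ICC near 0.0006, and the sample size section claims no such credit.

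**The trial may still resolve a 20% difference.** A reader might infer that it cannot. That goes too far: the article cites ICCs below 0.02, and power for 20% from 302 per 1000 is 61% at 0.02 and 86% at 0.01 (48% and 74% with a Poisson variance). The 20% claim depends on the ICC. The 10% claim fails at each of these values.

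**The remark about lower ICCs is right in direction.** A smaller ICC does raise power. The remark fails only because it starts from 10% as already achieved.

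A reader might also expect a null result to be taken as equivalence of the two interventions. No section plans such a claim, so the point does not rest on it.

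**Conclusion.** Wrong as written. The 89.2% and 97% statements and Table 3 are incompatible with an ICC of 0.05, 500 people per cluster and 12 against 12 clusters. At those inputs the two headline figures become about 11% and 21%, and none of the 12 cells is reached. For the 10% reduction at 302 per 1000, no reading tried that keeps the stated design effect exceeds about 25%. Separately, the 211 row is arithmetically inconsistent whatever the ICC.

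The size rests on three assumptions: annual incidence treated as a proportion (Poisson gives slightly less), the ideal allocation of 12 clusters per arm, and no credit for blocking or risk adjustment. How the printed figures were obtained cannot be determined from the article.

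**What to change.** - Recompute Table 3 and the two power statements for 12 against 12 clusters at ICC 0.05 and at a short range of lower residual ICCs, for example 0.02 and 0.01. Name the formula and the outcome scale.
- Show any credit for blocking or risk adjustment explicitly, as the residual ICC it is taken to produce.
- State the reduction detectable with 80% power at 302 per 1000: about 37% at ICC 0.05, 25% at 0.02 and 18% at 0.01.
- Reword the closing sentence on earlier ICCs: a lower ICC raises power, but at 0.02 power for a 10% reduction is still only about 20%.

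The cost is a recalculated table and a few sentences. Trial status reports that randomization is done and the trial is under way; the correction needs no extra clusters and no change of design. The downside is a much less favourable stated power.
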